## **8.6. Discontinuation/Withdrawal of Participants from Trial**

Each participant has the right to withdraw from any aspect of the trial at any time.

### **8.6.1. Withdrawal from Follow Up**

Participants may withdraw from the follow-up regime. If so, data up to the point of withdrawal will be collated and analysed accordingly.

### **8.6.2. Withdrawal of Consent**

Randomisation will be undertaken as close to the surgery as possible. Therefore, it is unlikely patients will withdraw consent prior to surgery. If they do, this will be recorded and they can discuss treatment options with their surgeon.

### **8.6.3. Change of Treatment**

For many reasons patients operations are cancelled, or patients withdraw themselves from the surgical waiting list. If patients have been randomised into the study and then do not go on to have surgery; reasons for cancellation/withdrawal will be recorded, if available and patients, if willing, will be followed up accordingly.

In the event of discontinuation or withdrawal from the trial the reason will be recorded on the Case Report Form (CRF). Analysis will be performed on an intention-to-treat basis.

## **8.7. Definition of End of Trial**

The end of trial is 12 months after the last participant was randomised and once all data has been collected and all queries resolved.

## **9. INVESTIGATIONAL MEDICINAL PRODUCT (IMP)**

### **9.1. IMP Description**

Both the trial drug and active control are injectable solutions which are manufactured commercially. They will be supplied to theatre packaged in their original packaging. Following randomisation, the anaesthetist will prepare the drug in a standardised fashion and offer the drug to the scrub nurse to draw up into a syringe ready for administration.

#### **9.1.1. Name of IMP:**

Liposomal bupivacaine (EXPAREL, Pacira Pharmaceuticals Inc., San Diego, California)

266mg Liposomal bupivacaine will be mixed with 100mg bupivacaine hydrochloride. The volume will then be expanded to 120ml with normal saline and administered as a single dose intra-operatively by periarticular infiltration.

The IMP will be supplied to sites free of charge by Pacira Pharmaceuticals Inc. Initial supplies will be ordered for each site by the Central Study Team following site initiation and confirmation from the Sponsor that all approvals are in place and the site is open to recruitment. For re-ordering of supplies, contact the Central study Team who will arrange further supplies.

#### **9.1.2. Control:**

Bupivacaine hydrochloride (must be plain, with no adrenaline/epinephrine present)

100mg bupivacaine hydrochloride alone. The volume will then be expanded to 120ml with normal saline and administered as a single dose intra-operatively by periarticular infiltration.

The bupivacaine used in the control arm will not be standardised by brand. The brand used will be what is available to the local participating trusts.

As per standard practice, 100mg Bupivacaine hydrochloride is a flat dose and will not be altered according to BMI in either the intervention or treatment arm.

### **9.2. IMP Administration**

The study drug will be administered using six 20 cc syringes with 21 or 22-gauge needles prior to wound closure.

Surgeons will be trained in the injection technique which will be as follows:

#### **9.2.1. Prior to implantation of definitive implants**

Syringe 1: Posterior capsule (8-10 injections medial and 8-10 injections lateral).

Syringe 2: Femur medial and lateral periosteum, posterior periosteum, suprapatellar/quadriceps tendon (20 injections).

Syringe 3: Tibia fat pad (5 injections); pes anserinus, medial collateral ligament, and gutter (15 injections).

Syringe 4: Circumferential periosteum (15-20 injections).

#### **9.2.2. After implantation of definitive implants**

Syringe 5: Midline quadriceps tendon (10 injections); retinaculum, medial gutter, femoral to tibia (10 injections).

Syringe 6: Lateral gutter, femoral to tibial (10 injections); subcutaneous/closure (10 injections).

Each injections should deliver approximately 1-1.5ml to the intended area. The tissue should visibly expand with minimal leakage.

### 9.3. Storage of IMP

Dependent on the standard practice and/or preference at each site, liposomal bupivacaine will be stored either in pharmacy or theatre refrigerators, temperature stipulated between 2°C and 8°C. Once removed from the refrigerator the drugs may be stored unopened at room temperature (20°C to 25°C) for up to 30 days but they should not be re-refrigerated. Vials should be visually inspected before use and must not be used if the stopper is bulging. Once opened, it must be used within 4 hours.

Bupivacaine hydrochloride should not be refrigerated or frozen as per the SmPC.

The appropriate pharmacy and/or theatre staff at all sites will be responsible for ensuring the drugs are kept at the correct temperature and where storage conditions are noted to be outside the recommended limits, the vials would need to be quarantined and disposed of as per standard practice at each site. Sites will be permitted to use their own temperature logs or one can be provided by the Oxford study office.

### 9.4. Compliance with Trial Treatment

The trial and control drugs are administered as a single intra-operative dose via peri-articular infiltration. As such, patient compliance with the treatment is not relevant in this study. However, surgical compliance with the intervention will be monitored on the Surgery CRF. Each treatment dose will be diluted to the same volume using normal saline as per the manufacturer's instructions. The injection technique of administration will be standardised and compliance with this confirmed on the Surgery CRF. Reasons for any deviation from the administration technique will also be recorded. The amount of drug administered will be recorded.

### 9.5. Accountability of the Trial Treatment

Accurate records of liposomal bupivacaine shipments, vials dispensed and destroyed must be maintained using the IMP Accountability Log provided in the Pharmacy File. This inventory record must be available for inspection at any time by the Trial Office. IMP supplies are to be used only in accordance with this protocol and under the supervision of the Investigator.

Accountability for the control drug will not be requested or monitored by the Trials Office.

### 9.6. Concomitant Medication

The trial and control drug are locally acting and no systemic interactions with other drugs have been reported. Local research teams will record any pain relief medication administered post-operatively. The opportunity to record any variants of the standard medications listed below will also be provided on the CRFs. Sites are not required to record concomitant medication outside of those listed below. Both the trial and control drug will be made up to volume using saline 0.9%. Liposomal bupivacaine must not be diluted with water or other hypotonic agents as it will result in disruption of the liposomal particles.

#### 9.6.1. Post-Operative Analgesia

Post-operative opioid consumption will be captured on the In-patient CRF. The management of post-operative pain may vary across each participating centre. Local post-operative analgesic regimes must be discussed and approved by the Chief Investigator prior to site activation.

**9.7. Post-trial Treatment**

The trial and control drugs are administered as a single intra-operative dose via peri-articular infiltration and no further doses of either of the drugs will be administered during the study period.

**10. SAFETY REPORTING****10.1. Definitions**

|                                               |                                                                                                                                                                                                                                                                                                                                                                                                                                                                                                                                                                                                                                                                                                                                                                                                                                                               |
|-----------------------------------------------|---------------------------------------------------------------------------------------------------------------------------------------------------------------------------------------------------------------------------------------------------------------------------------------------------------------------------------------------------------------------------------------------------------------------------------------------------------------------------------------------------------------------------------------------------------------------------------------------------------------------------------------------------------------------------------------------------------------------------------------------------------------------------------------------------------------------------------------------------------------|
| Adverse Event (AE)                            | Any untoward medical occurrence in a participant to whom a medicinal product has been administered, including occurrences which are not necessarily caused by or related to that product.                                                                                                                                                                                                                                                                                                                                                                                                                                                                                                                                                                                                                                                                     |
| Adverse Reaction (AR)                         | 
An untoward and unintended response in a participant to an investigational medicinal product which is related to any dose administered to that participant.
 
The phrase "response to an investigational medicinal product" means that a causal relationship between a trial medication and an AE is at least a reasonable possibility, i.e. the relationship cannot be ruled out.
 
All cases judged by either the reporting medically qualified professional or the Sponsor as having a reasonable suspected causal relationship to the trial medication qualify as adverse reactions.
                                                                                                                                                                                                                                                     |
| Serious Adverse Event (SAE)                   | 
A serious adverse event is any untoward medical occurrence that:
 
 
• results in death
 
• is life-threatening
 
• requires inpatient hospitalisation or prolongation of existing hospitalisation
 
• results in persistent or significant disability/incapacity
 
• consists of a congenital anomaly or birth defect.
 
 
Other 'important medical events' may also be considered serious if they jeopardise the participant or require an intervention to prevent one of the above consequences.
 
NOTE: The term "life-threatening" in the definition of "serious" refers to an event in which the participant was at risk of death at the time of the event; it does not refer to an event which hypothetically might have caused death if it were more severe.
 |
| Serious Adverse Reaction (SAR)                | An adverse event that is both serious and, in the opinion of the reporting Investigator, believed with reasonable probability to be due to one of the trial treatments, based on the information provided.                                                                                                                                                                                                                                                                                                                                                                                                                                                                                                                                                                                                                                                    |
| Suspected Unexpected Serious Adverse Reaction | A serious adverse reaction, the nature and severity of which is not consistent with the information about the medicinal product in                                                                                                                                                                                                                                                                                                                                                                                                                                                                                                                                                                                                                                                                                                                            |

|         |                                                                                                                                                                                                                                                                                                                                                       |
|---------|-------------------------------------------------------------------------------------------------------------------------------------------------------------------------------------------------------------------------------------------------------------------------------------------------------------------------------------------------------|
| (SUSAR) | 
question set out:
 
 
• in the case of a product with a marketing authorisation, in the summary of product characteristics (SmPC) for that product
 
• in the case of any other investigational medicinal product, in the investigator's brochure (IB) relating to the trial in question.
 
 |
|---------|-------------------------------------------------------------------------------------------------------------------------------------------------------------------------------------------------------------------------------------------------------------------------------------------------------------------------------------------------------|

517

518 NB: to avoid confusion or misunderstanding of the difference between the terms "serious" and "severe",  
 519 the following note of clarification is provided: "Severe" is often used to describe intensity of a specific  
 520 event, which may be of relatively minor medical significance. "Seriousness" is the regulatory definition  
 521 supplied above.

522 Any pregnancy occurring during the clinical trial and the outcome of the pregnancy should be recorded  
 523 and followed up for congenital abnormality or birth defect, at which point it would fall within the  
 524 definition of "serious".

## 525 10.2. Causality

526 The relationship of each SAE to the trial medication must be determined by a medically qualified  
 527 individual according to the following definitions:

528 **Reasonable possibility:** The adverse event follows a reasonable temporal sequence from trial medication  
 529 administration. It cannot reasonably be attributed to any other cause.

530 **No reasonable possibility:** The adverse event is probably produced by the participant's clinical state or  
 531 by other modes of therapy administered to the participant.

532 Assessment of causality (i.e. relatedness) will be recorded in the SAE form by the site PI or a delegate  
 533 (medically qualified doctor). In addition, this will be independently reviewed by a nominated clinician.

### 534 10.2.1 Events related to IMP administration during surgery

535 Expected events related to the administration of the trial drug (EXPAREL) into surgical sites have  
 536 been determined according to the FDA approved US Prescribing Information, found in the Appendix  
 537 A of the IMPD or here: [www.dailymed.nlm.nih.gov](http://www.dailymed.nlm.nih.gov). This will be used as the Reference Safety  
 538 Information (RSI) for all safety assessments and reporting, including SUSARs.

539 Reported AEs occur at a similar rate as the corresponding bupivacaine hydrochloride controls in the  
 540 active comparator studies.

541 The surgery and the administration of the drugs are integrated components of the treatment arms.  
 542 Events may not be linked to one specific component, however, those expected events related to  
 543 knee replacement surgery are discussed in 10.2.2.

544 The most common adverse reactions (incidence greater than or equal to 10%) following EXPAREL  
 545 administration in surgical sites were nausea, constipation, and vomiting.

546 The common adverse reactions (incidence greater than or equal to 2% to less than 10%) following  
 547 EXPAREL administration were pyrexia, dizziness, edema peripheral, anemia, hypotension, pruritus,

tachycardia, headache, insomnia, anemia postoperative, muscle spasms, hemorrhagic anemia, back pain, somnolence, and procedural pain.

The less common/rare adverse reactions (incidence less than 2%) following EXPAREL administration were chills, erythema, bradycardia, anxiety, urinary retention, pain, edema, tremor, dizziness postural, paresthesia, syncope, incision site edema, procedural hypertension, procedural hypotension, procedural nausea, muscular weakness, neck pain, pruritus generalized, rash pruritic, hyperhidrosis, cold sweat, urticaria, bradycardia, palpitations, sinus bradycardia, supraventricular extrasystoles, ventricular extrasystoles, ventricular tachycardia, hypertension, pallor, anxiety, confusional state, depression, agitation, restlessness, hypoxia, laryngospasm, apnea, respiratory depression, respiratory failure, body temperature increased, blood pressure increased, blood pressure decreased, oxygen saturation decreased, urinary incontinence, vision blurred, tinnitus, drug hypersensitivity, and hypersensitivity.

## **10.2.2 Events Related to Knee Replacement Surgery**

There will be many events expected in this patient population that are related specifically to their knee replacement surgery and the perioperative care they receive. All knee replacement procedures whether primary surgery or revision procedures carry a risk of death, morbidity including wound infection, bleeding intra and post operatively, thrombo-embolic complications and complications secondary to existing co-morbidity e.g. ischaemic heart disease [31].

Specific complications following knee replacement procedures include loosening of components – Tibia/Femur/both, dislocation of knee/bearing, superficial and deep infection, unexplained knee pain, knee stiffness, haematoma, mechanical failure of replacement, periprosthetic fracture. These complications may result in the need for further surgery such as revision operations, arthroscopy, washout, manipulation under anaesthetic, debridement (open), aspiration, above knee amputation, patella resurfacing [31].

Any expected complications outlined above will be documented on the Adverse Event form. If any complications become serious (i.e. meets the SAE criteria) the SAE CRF will be completed accordingly.

All SAEs will be coded using MedDRA. SAEs related to knee replacement surgery will be coded as a post-operative complication.

## **10.3. Procedures for Recording Adverse Events & Reporting Serious Adverse Events**

Within 30 days of the surgery, Adverse Events need to be recorded if there is a reasonable possibility they are related to the:

- Administration of the IMP or control drug
- Knee replacement surgery

These will be recorded on Adverse Event form.

If the Adverse Event is deemed to be serious (i.e. meets the SAE criteria) then this will be reported on the SAE form. Serious Adverse Events must be reported throughout the duration of the study and follow up period (12months). The sites must notify the study office in Oxford of these events within 24 hours

586 following knowledge of the event. The completed form will be sent to the Oxford study office via secure  
587 nhs.net email ([[contact]](mailto:[contact])).

588 All patient deaths, regardless of cause/relatedness, will need to be reported on the SAE form.

589 Centres will routinely monitor patient records for any events that may have been missed.

590 The study office in Oxford will perform an initial check of SAE reports, request any additional  
591 information, and ensure it is reviewed by the trial's nominated person in a timely manner and according  
592 to the relevant SOP on safety reporting. The nominated person will also perform an independent review  
593 of the causality.

594 SAEs considered related to the trial medication as judged by a medically qualified investigator or the  
595 Sponsor will be followed either until resolution, or when the *event* is considered stable.

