### **8.3. Randomisation, Blinding and Code-breaking**

Randomisation will be performed locally by the trial site using a secure online internet based system (RRAMP) provided by the Oxford Clinical Trials Research Unit (OCTRU).

Patients will be randomised 1:1 to the two treatment groups using stratified randomisation with variable block sizes, stratified by trial hospital and surgical procedure (TKR or UKR).

Due to local patient pathways, informed consent and baseline assessments may be completed at the same hospital visit however, it may be the case randomisation is not performed on the same day. Where possible, randomisation will occur on the day of surgery either by a member of the clinical research team or a member of the surgical team, where this is not possible randomisation may occur on the days prior to surgery to allow for time to coordinate the drug supplies and inform the operative and anaesthetic team. If consent has occurred more than a day before randomisation, the local research team will verbally check the patient still agrees to participation before proceeding with randomisation.

Only trial team members listed on the delegation log are authorised to perform randomisations.

Patients will be blinded to the treatment allocation. Trial sites should make every effort to ensure that patient blinding is maintained throughout the duration of the trial so that no bias is introduced. The arrangements for maintaining patient blinding for the trial should be considered in detail and those arrangements carefully planned, documented and communicated to ensure accidental unblinding is avoided.

Methods for ensuring patient blinding should be discussed during the Site Initiation Visits, and may include only recording the drug given (active/control) in the surgeon notes as "as per protocol of SPAARK trial" but the actual drug given recorded in the anaesthetic chart. Local practice may vary and the trial sites can discuss with the central study team alternative ways to ensure that patient blinding is maintained.

Unblinding will be performed on an individual basis as clinical need dictates.

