#### 3.2 Randomisation and Blinding

Randomisation between intervention and control will be 1:1, and will be stratified by study centre and operation type (Total Knee Replacement (TKR) or Unicompartmental Knee Replacement (UKR)). Randomisation will be performed using the RRAMP internet system provided by the Oxford Clinical Trials Research Unit (OCTRU). Where possible, randomisation will occur in theatre at the time of surgery either by a member of the clinical research team or a member of the surgical team. If not possible, randomisation can occur on days prior to the surgery to allow for time to coordinate the drug supplies and inform the operative and anaesthetic team. If consent has occurred more than a day before randomisation, the local research team will verbally check the patient still agrees to participation before proceeding with randomisation.

Full details of the randomisation are available in SPAARK\_RBP\_v3.0\_19Apr2018, stored in the confidential statistical section of the TMF.

The patient will be blinded to the treatment allocation. Unblinding will be performed on an individual basis as clinical need dictates. Surgeons who administer the medication cannot be blinded to treatment allocation; however, blinding of surgeons and outcome assessors is not necessary as the two co-primary outcomes are patient reported measures.

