#### 6.7 Harms

A serious adverse event (SAE) is any untoward medical occurrence that results in death, is life-threatening, requires inpatient hospitalisation or prolongation of existing hospitalisation, results in persistent or significant disability/incapacity, consists of a congenital anomaly or birth defect or is otherwise considered medically significant by the investigator.

Any adverse event (AE) occurring within 30 days of surgery will be recorded if there is a reasonable possibility it is related to either: (i) the administration of the investigational medical product (IMP) or the

control drug; or (ii) the knee replacement surgery. Expectedness and causality of AEs and SAEs will also be determined. AEs occurring more than 30 days following surgery will only be recorded if (i) the event is deemed to be serious (meets SAE criteria) and there is a reasonable possibility it is related to the knee replacement surgery; or (ii) there is a patient death.

Details of expected events related to either the administration of the IMP during surgery or the knee replacement surgery itself are provided in the trial protocol. It is noted that reported AEs related to the IMP have been shown to occur at a similar rate as those in the corresponding bupivacaine hydrochloride controls in active comparator studies.

The number of AEs occurring up to 30 days post-surgery will be reported by treatment group. The number of participants experiencing an AE will also be reported by treatment group, and the two groups will be compared. The number of SAEs, SARs, and SUSARs occurring up to 12 months post-randomisation will be reported by treatment group (Table 15). The numbers of participants experiencing an SAE, SAR or SUSAR will also be summarised by treatment group and will be compared between the liposomal bupivacaine + bupivacaine hydrochloride and bupivacaine hydrochloride alone groups by examination of the 95% confidence intervals for the difference in incidence. The analysis will be conducted for the ITT population as defined in Section 7. The number of deaths per arm will also be compared. Descriptive data on the type of AE reported, as well as MedDRA codes for the SAEs will also be presented.

**Table 15:** Summary of Serious Adverse Events (SAEs) including SARs/SUSARs

|                                                                        | Intervention | Control | Total |

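### Relatedness judged by staff who may know the allocation decides which non-serious AEs are recorded and which SAEs count as SARs, so those between-arm comparisons are open to attribution bias

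*Combined protocol and SAP*

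**What the plan says.** **Recording.** Protocol 10.3: "Within 30 days of the surgery, Adverse Events need to be recorded if there is a reasonable possibility they are related to the" administered trial or control drug, or to the operation. SAP 6.7 repeats this filter. Under Protocol 10.3, SAEs are reportable for the full 12 months with no relatedness condition.

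**Causality.** Protocol 10.2: "Assessment of causality (i.e. relatedness) will be recorded in the SAE form by the site PI or a delegate", who must be a doctor. It continues: "In addition, this will be independently reviewed by a nominated clinician". Protocol 10.1 defines an SAR by the opinion of the reporting investigator.

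**Blinding.** SAP 3.2: "Surgeons who administer the medication cannot be blinded to treatment allocation; however, blinding of surgeons and outcome assessors is not necessary", because the two co-primary outcomes are patient-reported. Protocol 6.1 and SAP 5.4 give the same reason. Protocol 8.3 suggests keeping the allocation out of the surgeon's notes, "but the actual drug given recorded in the anaesthetic chart".

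**Analysis.** Related AEs to 30 days are a listed secondary endpoint (Protocol 5, SAP Table 1). SAP 6.7: "The number of participants experiencing an AE will also be reported by treatment group, and the two groups will be compared". It also compares participants with SAEs, SARs and SUSARs through 95% confidence intervals for the difference in incidence.

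**The concern.** The argument for leaving assessors unblinded is sound for a score that a blinded patient fills in. It says nothing about an endpoint that exists only once a member of staff has decided what caused an event. For non-serious AEs that decision governs whether the event enters the database. For SAEs it governs whether the event is counted as an SAR.

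There is real room for discretion. Protocol 10.2.1 says the commonest reactions after EXPAREL "administration in surgical sites were nausea, constipation, and vomiting". Protocol section 4 names nausea and vomiting, with pruritus, drowsiness and hypotension, as opioid side effects, and most of these also appear among the EXPAREL reactions. The relatedness test is itself inconsistent. The adverse reaction definition in 10.1 asks only that a relationship not be excluded, whereas 10.2 asks that no other cause reasonably explain the event.

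If knowledge of the arm shifts that judgement, the AE and SAR comparisons mix drug effect with attribution, for a product the protocol describes as unlicensed in the UK. A non-serious AE that was never written down cannot be re-adjudicated later.

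**Working it through.** **Step 1. Which safety counts depend on a judgement that may be unblinded?**

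| Count in SAP 6.7 | Relatedness judgement needed? | Judge stated to be blinded? | Re-adjudicable later? |
|---|---|---|---|
| Non-serious AEs to 30 days | Yes, to be recorded at all | No | Not if unrecorded |
| SARs | Yes, to be classified | No (site doctor or second reviewer) | Yes, an SAE form exists |
| All SAEs, following Protocol 10.3 | No | Not applicable | Yes |
| SAEs after 30 days, following SAP 6.7 | Yes: related to the surgery, or a death | No | Not if unrecorded |

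The last two rows conflict: the protocol collects every SAE to 12 months, while the SAP narrows those after 30 days.

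**Step 2. Number per arm.** For the QoR-40, n = 2(2.2414 + 1.2816)² × 15.5² / 5² = 238.5, so 239 per arm. The plan states 240, which agrees. Then 240 / (1 − 0.04) = 250. Only the 250 is used below.

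**Step 3. Illustration for non-serious AEs.** The documents give no AE or recording rates, so every rate here is assumed. Let the true incidence t be equal in both arms, and let q be the share of participants with an event for whom it is judged related and recorded.

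- Recorded risk = t × q.
- SE = √[p₁(1 − p₁)/250 + p₂(1 − p₂)/250].
- Chance that the 95% CI excludes zero = Φ(d/SE − 1.96) + Φ(−d/SE − 1.96), where d is the difference in recorded risk.

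SAP 6.7 ties the 95% CI to SAEs, SARs and SUSARs and names no method for AEs. Using it for AEs is also an assumption.

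Worked case with t = 40% and q = 60% versus 50%: recorded risks are 24% and 20%, so d = 0.04. SE = √(0.0007296 + 0.00064) = 0.0370 and d/SE = 1.08. The chance is 19.1%, against a nominal 5%.

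| q, intervention vs control | Recorded risk ratio | t = 20% | t = 40% | t = 60% |
|---|---|---|---|---|
| 50% vs 50% | 1.0 | 5% | 5% | 5% |
| 55% vs 50% | 1.1 | 6.5% | 8.5% | 11.2% |
| 60% vs 50% | 1.2 | 11.0% | 19.1% | 29.8% |
| 70% vs 50% | 1.4 | 28.1% | 55.7% | 80.4% |

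The last three columns give the chance of a CI excluding zero with no drug effect. Swapping the arms gives the same chances with the ratio inverted (1.2 becomes 0.83), so a true excess could equally be hidden.

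**Step 4. Illustration for SARs.** Assume 10% of participants have one SAE: 250 × 0.10 = 25 per arm. If 10% of these are judged related in control and 20% in the intervention arm, the expected SARs are 2.5 and 5. The all-cause SAE counts stay equal at 25.

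**The case against.** There is a fair case on the other side.

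- Relation to the surgery alone is enough for recording, and that route is the same in both arms. Protocol 10.2.2 speaks of surgery together with perioperative care, so nausea put down to post-operative opioids might be recorded anyway. This narrows the filter but does not close it: nausea, constipation and vomiting are not among the complications that 10.2.2 names for the AE form.
- Centres check records for missed events, and SAE causality gets a second review. Both help. Neither is stated to be blinded, and the second review is described only for SAEs.
- Surgeons cannot be blinded, as SAP 3.2 says. That stands for surgeons. It does not explain why no other judge of relatedness is blinded.
- Safety is secondary, and secondary analyses are treated as supportive. That limits the consequences but does not remove the bias.

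A reader might infer more than the documents support:

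- *That every person recording AEs knows the arm.* Knowledge is permitted, not stated for each recorder.
- *That staff hold an expected-reaction list for EXPAREL only.* The itemised list in 10.2.1 is framed that way, but Protocol 10.4 says the reference safety information covers the control as well.
- *That SARs are lost for good.* Under Protocol 10.3 all SAEs have a form, so their causality can be judged again.

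**Conclusion.** The concern holds for two comparisons: participants with non-serious AEs, and participants with SARs. Both depend on a causality judgement by staff who may know the allocation, and the reason given for unblinded assessment does not apply to them. The all-cause SAE comparison is largely protected, provided the protocol's collection rule is the one followed. Protocol 10.3 and SAP 6.7 must be reconciled on SAEs after 30 days.

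The size and direction of any bias cannot be derived from the documents. The figures above show only that, at 250 per arm, modest differences in recording could matter. It would be wrong to conclude that the AE results are in fact biased, or that they favour either arm. The primary outcomes are not touched by this point.

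**What to change.** 1. **Patient-reported symptoms, whatever the cause.** At the day 0 to 3 assessments in Protocol 8.5, including the telephone contacts after early discharge in 6.3, ask the blinded patient yes or no for nausea, constipation and vomiting, the three reactions that 10.2.1 lists at 10% or more. Add their comparison by arm to SAP 6.7. Cost: slightly longer forms and calls, with no new visits. This covers the first three days only. Other AEs, and those from day 4 to day 30, remain filtered and should be reported with that caveat.

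2. **A parallel blinded SAR count.** Have the existing nominated clinician make an initial causality judgement from an SAE report with the allocation removed. In SAP Table 15, show SAR counts on that judgement beside the investigator-defined counts. Leave the SAR definition and regulatory reporting unchanged. Cost: redacting each SAE packet. The count should not replace the investigator's, because a blinded judge cannot use formulation-specific timing. Section 4 gives bupivacaine a half-life of 120 to 240 minutes and the liposomal form a reported effect of up to 72 hours, and 10.2 requires a plausible time sequence.

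3. **Main serious-event comparison.** Name all-cause SAEs as the main between-arm comparison of serious events, and reconcile Protocol 10.3 with SAP 6.7 on which SAEs are collected after 30 days. Cost: a wording change.
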